**Figure 3 figure3:**
[figure not shown]
Study design.

### Participants

We aim to include a total of 60 participants: 30 in cohort 1 and 30 in cohort 2. The number of participants is based on the 10-times rule, a widely used minimum-sample-size estimation method for partial least squares structural equation modeling (PLS-SEM) [32]. This method was discussed with a statistician. In addition, we considered the current practices in the field [12], the explorative nature of this study, and the staff available to provide support.

Participants will be considered eligible if they are aged 65 years or older, are not in paid employment, and live alone independently at home. These inclusion criteria fit a potential target audience of almost 1 million people [33]. In addition to these criteria, participants need to speak Dutch to use the app, should be able to use a tablet or computer by themselves, and should have a wireless internet connection at home, which is required for the app. The latter 2 criteria seem feasible, as 94.5% of all older Dutch adults aged 65-75 years have internet access at home, with 77% using the internet daily [34]. Apart from willingness to provide informed consent, there are no exclusion criteria.

### Recruitment

The project members will recruit participants via different routes. An email will be sent out to an existing online panel of older adults (*Ouderenpanel*). Flyers will be distributed in neighborhoods, community centers, sports canteens, and other settings frequently attended by older adults. Advertorials will be placed in local and community newspapers and on social media. Both the flyers and the advertorials will contain a short link to the PACO website with more information and the form to sign up. Lastly, participants will be encouraged to invite relatives.

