## Methods

### Study Design

An unblinded randomized controlled trial will be carried out. At the time of study protocol submission, all preparations have been made to start recruitment. There will be 2 cohorts (Figure 3). Participants in the first cohort will receive the 8-week PACO app immediately. Participants in the second cohort will receive the PACO app after a 4-week waiting-list condition and serve as a control group. A combination of various data collection methods will be used for this study, including questionnaires (control, at intake, T0, T1, and T2), data log collection during the intervention period, and an optional interview afterward. The T0 questionnaire will mark the start of the intervention, T1 will be completed after 4 weeks of use, and T2 after 8 weeks of use (Figure 3).

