### Procedure

Interested people can visit a website to view more information, or they can contact the researchers. People can choose to receive the information letter and consent form by post (Multimedia Appendix 1) or view and complete the form online. After providing informed consent, participants will be invited to complete the intake questionnaire. In this questionnaire, they will be asked to report their demographics (gender, age, educational level, health conditions, risk of malnutrition [35], and eHealth literacy [36]), whether they own a device to use for the study, and their motivation to participate. A copy of the signed informed consent will be sent to all participants by mail. The researchers will mail people who do not return the informed consent by post to check whether something has gone wrong or they do not wish to participate (no explanation will be required).

After completing both the informed consent and the intake questionnaire, participants will be assigned a random 4-digit research number. To allocate participants to a cohort, they will be randomly assigned a digit, either 1 or 2, in a list generated by Excel (version 16.0.13426.20274; Microsoft). Participants will receive an email from author LK containing their research number, information on their allocated cohort, and a copy of the information letter and the signed informed consent.

Participants in cohort 2 will first be asked to complete the additional control questionnaire (Table 1) and will start the intervention period after 4 weeks. At the start of the intervention period, participants will receive an email with instructions for the onboarding process. The email will contain a video message from the researchers introducing themselves and the project, as well as a link to the freely available PACO website. Once participants have created an account, they will be asked to complete the T0 questionnaire, assessing the health parameters and relationship with the ECA. Participants will be phoned within 2 working days and asked whether they have any questions. If a participant does not wish to be called, this can be indicated by email. If a participant needs help, the researchers will offer to visit the participant. A logbook will be kept of all such contacts. If participants do not have a tablet or a computer, they will be given a tablet for the duration of the study.

**Table 1 table1:** Metadata and factors measured via questionnaires, per study phase.

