### Limitations

Like any evaluation plan, ours has some limitations. The first limitation relates to our recruitment strategy. We expect to include more women than men. In previous studies [44], we found women to be more interested in lifestyle-related studies, resulting in focus group sessions with an overrepresentation of women. However, given that there are more single women than men in older age groups in the Netherlands [61], a majority of women is a realistic reflection of society. Another aspect of our recruitment strategy is that participants are encouraged to invite relatives, and this might induce a risk of contamination. If a closely related person joins the study, we will monitor this meticulously to see whether contamination takes place, and whether and how it influences our results.

Second, use of the ECA intervention might be influenced by the study itself. Participants know that they are expected to complete multiple questionnaires and will be called by phone if they do not use the app for 7 days. Thus, participants might be inclined to use the app more often than if the intervention were applied outside a randomized controlled trial setting. However, in order to understand the determinants affecting use and health effects, the questionnaires are essential, and a phone call is needed to ensure that there are no technical issues influencing use.

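### Inviting relatives while allocating each person individually splits about half of any linked pairs, so the wait-list control can be contaminated; the plan only monitors this

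*Protocol article*

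**What the plan says.** All references are to the protocol article.

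- **Recruitment** lists a panel email, flyers and advertorials, and ends: "Lastly, participants will be encouraged to invite relatives".
- **Procedure** describes the allocation: "To allocate participants to a cohort, they will be randomly assigned a digit, either 1 or 2, in a list generated by Excel". It gives no separate rule for people who know each other.
- **Participants** sets the target: "We aim to include a total of 60 participants: 30 in cohort 1 and 30 in cohort 2".
- **Study Design** calls the trial unblinded and defines the control: "Participants in the second cohort will receive the PACO app after a 4-week waiting-list condition and serve as a control group".
- **Limitations** acknowledges that inviting relatives carries a risk of contamination and responds: "If a closely related person joins the study, we will monitor this meticulously to see whether contamination takes place". The same sentence says the team will also look at whether and how it affects the results.
- **Data Analysis** compares control, T0, T1 and T2 by within-subject t tests. It does not mention linked participants.
- **Procedure** has the onboarding email go out at the start of the intervention period with an introductory video, "as well as a link to the freely available PACO website". Participants then create an account and complete T0.

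**The concern.** The recruitment route creates linked people, and the allocation method then ignores the link. In a split pair, one relative has recipes, social tips, stories and social goals from the app while the other is meant to be untreated. Food ideas pass easily between relatives. Loneliness, a main outcome, can also change in the waiting relative simply because the other acts on a social goal and makes contact.

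The 4-week wait is the trial's only untreated period. If some waiting participants are exposed, two things happen. First, cohort 2's control-to-T0 change picks up part of the app's effect and looks like change without treatment. Second, cohort 2's T0 values are already shifted, so later change measured from T0 is smaller. If the exposure acts in the same direction as the app, both errors pull toward no effect, as does the dilution of any contrast between the cohorts. Watching for contamination leaves the bias in place once it has occurred.

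**Working it through.** **The plan's own figure.** The target is 60 = 30 + 30. The article gives its basis as follows: "The number of participants is based on the 10-times rule, a widely used minimum-sample-size estimation method". That derivation depends on the path diagrams, which are not shown in the text available, so it is neither confirmed nor rejected here. The point below uses only the 30 per cohort.

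**Step 1: chance that a pair is split.** With independent draws of 1 or 2, P(split) = 0.5. If the list is forced to exactly 30/30, P(split) = 30/59 = 0.508. The result hardly depends on how the list was made.

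**Step 2: chance of at least one split among k pairs.** P = 1 − 0.5^k. For k = 3 this is 1 − 0.125 = 87.5%. For k = 5 it is 1 − 0.031 = 96.9%.

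**Step 3: share of the wait-list exposed.** Each split pair has exactly one waiting member, so the expected number at risk is k/2. As a share of 30 controls this is (k/2)/30 = k/60, if every split pair leads to exposure.

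| Pairs k (assumed) | Participants in pairs | Expected split pairs | Share of 30 controls exposed |
|---|---|---|---|
| 1 | 2 of 60 | 0.5 | 1.7% |
| 5 | 10 of 60 | 2.5 | 8.3% |
| 10 | 20 of 60 | 5 | 16.7% |

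The number of pairs is an assumption throughout. For a given k the last column is an upper figure: some split pairs will share nothing, and some will not overlap in time.

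**Step 4: which comparisons are affected.**

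| Comparison | Affected by exposure during the wait? |
|---|---|
| Cohort 1, T0 to T1 to T2 | Largely not: these people have the app throughout |
| Cohort 2, control to T0 | Yes: this is the waiting period itself |
| Cohort 2, T0 to T1 and T2 | Yes, through a shifted T0 |
| Cohort 1 against cohort 2 over the first 4 weeks | Yes, if such a contrast is made |

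**Step 5: cohort sizes, if the list is a simple draw.** P(exactly 30/30) = C(60,30)/2^60 = 0.103, about 10%.

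**Step 6: statistical cost of allocating linked people together.** With a share s of participants in pairs and intraclass correlation ρ, the variance factor is 1 + sρ. For assumed s from 0.10 to 0.50 and ρ from 0.05 to 0.30, it runs from 1 + 0.10 × 0.05 = 1.005 to 1 + 0.50 × 0.30 = 1.15. To hold precision, 60 would become 60 × 1.005 = 60.3 (61 rounded up) to 60 × 1.15 = 69.

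**The case against.** The authors did see the risk. They name it, and their monitoring includes an assessment of its influence on the results. An eligible relative must also be 65 or older, out of paid work and living alone, so pairs may be few and will not share a household. Relatives are the last of several recruitment routes, the wait is only 4 weeks, and the study is described as explorative. All of this stands. It limits the likely size and rules out saying that the wait-list *is* contaminated. It does not turn monitoring into prevention.

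Some stronger readings are tempting, but the article does not support them:

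- **That the app is open to people on the wait-list.** The wording about the website may mean free of charge. The onboarding link is sent when the intervention period starts, an account is needed, and the logs hold user ID and time. Open access is not shown.
- **That a given share of exposed controls costs a fixed share of the trial's information.** That calculation needs a two-arm contrast with full effect in every exposed control. The stated test is within-subject, and exposure may be partial.
- **That ignoring relatedness must make standard errors too small.** In a between-cohort contrast under individual allocation, same-cohort pairs raise the variance and split pairs lower it, so the two roughly cancel. In within-subject tests the direction can hold if relatives' changes are positively correlated, but the factor is modest (Step 6).
- **That the allocation is certainly a simple draw.** A shuffled list of 30 ones and 30 twos also fits the text, so the 10% figure is conditional.

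Finally, joint allocation has a cost of its own: a relative who joins later can foresee the cohort. That is a real drawback and is addressed in the fix.

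**Conclusion.** The concern holds in a limited form. Encouraging relatives to join while allocating individually would split about half of any linked pairs (50%, or 50.8% if 30/30 is forced), and the stated response cannot prevent or reverse the exposure. The wait-list can therefore be contaminated. The effect would fall mainly on cohort 2's control-to-T0 change, its T0 baseline and any between-cohort contrast, and would be toward no effect. Cohort 1's T0–T2 change is largely safe.

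The size cannot be fixed from the article. It would be about 2% of controls for one pair, 8% for five and 17% for ten, assuming that every split pair exposes its waiting member. The direction assumes that exposure works the same way as the app. This is a weakness with an inexpensive remedy, and it does not invalidate the trial.

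**What to change.** 1. **Record links.** Ask at sign-up whether the person was invited by a participant, and record the inviter's research number.
2. **Allocate linked people as one unit.** An inviter and relatives who sign up together get one draw. A relative who joins after the inviter has been allocated goes to the inviter's cohort.
3. **Account for linked units in the analysis**, for example with unit-clustered standard errors.
4. **Prespecify a sensitivity analysis excluding invited relatives**, because the cohort of late joiners is predictable. It also covers a residual case: if start dates are individual, a late relative placed in cohort 2 may still be waiting when the inviter is already using the app.
5. **Open PACO accounts only from the allocated start date**, and state this in the protocol.
6. **State how the Excel list is made.** If it is a simple draw, replace it with a concealed list in blocks of random size, applied to units, so that the cohorts come out near 30/30.

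The cost is one sign-up field, an account check, possibly a new list, and a small loss of precision (variance factor about 1.005 to 1.15 under the assumptions in Step 6). The named downside is the predictable allocation of later relatives. A simpler alternative is to stop inviting relatives; it needs no statistical adjustment and costs only the recruits that route would have brought.

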### Procedure

Interested people can visit a website to view more information, or they can contact the researchers. People can choose to receive the information letter and consent form by post (Multimedia Appendix 1) or view and complete the form online. After providing informed consent, participants will be invited to complete the intake questionnaire. In this questionnaire, they will be asked to report their demographics (gender, age, educational level, health conditions, risk of malnutrition [35], and eHealth literacy [36]), whether they own a device to use for the study, and their motivation to participate. A copy of the signed informed consent will be sent to all participants by mail. The researchers will mail people who do not return the informed consent by post to check whether something has gone wrong or they do not wish to participate (no explanation will be required).

After completing both the informed consent and the intake questionnaire, participants will be assigned a random 4-digit research number. To allocate participants to a cohort, they will be randomly assigned a digit, either 1 or 2, in a list generated by Excel (version 16.0.13426.20274; Microsoft). Participants will receive an email from author LK containing their research number, information on their allocated cohort, and a copy of the information letter and the signed informed consent.

Participants in cohort 2 will first be asked to complete the additional control questionnaire (Table 1) and will start the intervention period after 4 weeks. At the start of the intervention period, participants will receive an email with instructions for the onboarding process. The email will contain a video message from the researchers introducing themselves and the project, as well as a link to the freely available PACO website. Once participants have created an account, they will be asked to complete the T0 questionnaire, assessing the health parameters and relationship with the ECA. Participants will be phoned within 2 working days and asked whether they have any questions. If a participant does not wish to be called, this can be indicated by email. If a participant needs help, the researchers will offer to visit the participant. A logbook will be kept of all such contacts. If participants do not have a tablet or a computer, they will be given a tablet for the duration of the study.

**Table 1 table1:** Metadata and factors measured via questionnaires, per study phase.

Metadata and factors			Questionnaires						
			Control		T0		T1		T2

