**Methods:**

The web-based eHealth app PACO is a fully automated 8-week intervention in which 2 ECAs engage older adults in dialogue to motivate them to change their dietary behavior and decrease their loneliness. PACO was developed via a human-centered and stakeholder-inclusive design approach and incorporates Self-determination Theory and various behavior change techniques. For this study, an unblinded randomized controlled trial will be performed. There will be 2 cohorts, with 30 participants per cohort. Participants in the first cohort will immediately receive the PACO app for 8 weeks, while participants in the second cohort receive the PACO app after a waiting-list condition of 4 weeks. Participants will be recruited via social media, an online panel, flyers, and advertorials. To be eligible, participants must be at least 65 years of age, must not be in paid employment, and must live alone independently at home. Primary outcomes will be self-assessed via online questionnaires at intake, control, after 4 weeks, and after 8 weeks, and will include eating behavior and loneliness. In addition, the primary outcome—use—will be measured via data logs. Secondary outcomes will be measured at the same junctures, via either validated, self-assessed, online questionnaires or an optional interview.

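### By the Procedure and Table 1, loneliness and eating behaviour are first measured after the cohort is known, and T0, cohort 2's only end-of-wait measurement, is requested only from people who create a PACO account

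*Protocol article*

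**What the plan says.** The Procedure section gives the sequence.

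- **Intake.** After consent, participants complete the intake questionnaire, in which "they will be asked to report their demographics (gender, age, educational level, health conditions, risk of malnutrition [35], and eHealth literacy [36"; the same sentence adds device ownership and motivation to take part. No loneliness scale and no eating recall is listed.
- **Allocation.** "After completing both the informed consent and the intake questionnaire, participants will be assigned a random 4-digit research number". A digit of 1 or 2 from an Excel list then sets the cohort.
- **Disclosure.** Participants receive an email "containing their research number, information on their allocated cohort, and a copy of the information letter and the signed informed consent".
- **Cohort 2 only.** "Participants in cohort 2 will first be asked to complete the additional control questionnaire (Table 1) and will start the intervention period after 4 weeks".
- **Both cohorts, at the start of their intervention period.** An onboarding email brings a link to the PACO website and a video message. "Once participants have created an account, they will be asked to complete the T0 questionnaire, assessing the health parameters and relationship with the ECA".

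Table 1 has columns for Control, T0, T1 and T2 and none for intake. Eating behavior and loneliness are ticked in all four columns.

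The abstract says otherwise: "Primary outcomes will be self-assessed via online questionnaires at intake, control, after 4 weeks, and after 8 weeks, and will include eating behavior and loneliness". The Study Design section names control, intake, T0, T1 and T2 as separate questionnaires.

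The Data Analysis section states a within-subject t test between control, T0, T1 and T2. It also says that a participant with no PACO interaction for 14 consecutive days is treated as a dropout and omitted from further analysis.

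**The concern.** Both health outcomes are self-reported and the trial is unblinded. A baseline taken after people know their cohort can be coloured by that knowledge. Here it is also taken at a different step in each cohort: cohort 2 answers having just learned that it must wait, cohort 1 having been onboarded and having opened an account.

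The second problem is who is asked for T0. The Study Design section makes cohort 2 the control group, and its control information is the change over the 4-week wait, from the control questionnaire to T0. If T0 reaches only people who open an account at the end of the wait, the control follow-up is conditional on taking up the intervention. In cohort 1, a person who never opens an account has no baseline at all. Outcome data that were never collected before allocation cannot be recovered later.

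**Working it through.** **Step 1: where the outcome items sit.** Table 3 gives loneliness 6 items, need satisfaction 24, quality of life 13 and the Rapport Scale 10. The Data Collection section gives 3 eating questions, 9 open user-experience questions and 2 willingness-to-pay questions. The use scales in Table 3 have 10, 4, 5, 4, 4 and 3 items.

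- Control: 6 + 24 + 13 + 3 = 46
- T0: 46 + 10 = 56
- T1: 56 + 9 = 65
- T2: 56 + (10 + 4 + 5 + 4 + 4 + 3) + 2 = 56 + 30 + 2 = 88

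Table 1 prints 46, 56, 65 and 88, so all four reproduce. The control questionnaire is exactly the health battery, and T0 is that battery plus the Rapport Scale. Of the 56 T0 items, only 10 concern the agent; the other 46 need no app.

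**Step 2: the order in each cohort, from the Procedure.**

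| | Cohort 1 | Cohort 2 |
|---|---|---|
| First health measurement | T0 | Control questionnaire |
| Cohort already disclosed? | Yes | Yes |
| Account needed? | Yes | No |
| Role of T0 | Only baseline | Only end-of-wait measurement |

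The account condition therefore affects cohort 1's baseline and cohort 2's end-of-wait value. It does not affect cohort 2's baseline.

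**Step 3: can the abstract be reconciled by reading intake as T0?** Its four occasions would then match Table 1's four columns. But the Study Design section lists intake and T0 separately, and the Procedure puts intake before allocation and T0 after it. The conflict remains.

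**Step 4: what missing T0 does to the stated test.** Let q be the share of cohort 2 without T0, and let C and N be the mean control-to-T0 change in people with and without an account. The mean change over all of cohort 2 is (1 − q)C + qN. The paired test sees only C. The bias is C − [(1 − q)C + qN] = q(C − N). A difference in level between the two groups drops out, because people without T0 leave both sides of the pair. Only a difference in change remains.

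**Step 5: what it does to a week-4 comparison between cohorts** (cohort 1 at T1 against cohort 2 at T0), which the article does not state. Here a level difference of D SD would shift the observed cohort 2 mean by q × D. The protocol gives neither value, so these are assumed:

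- q = 10% (27 of 30 with T0), D = 0.25 to 0.8: 0.025 to 0.08 SD
- q = 20% (24 of 30): 0.05 to 0.16 SD
- q = 30% (21 of 30): 0.075 to 0.24 SD

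These are illustrations, not estimates. On the Procedure's sequence cohort 1 also passes through account creation before T1, so part of the shift could cancel. How much is unknown, because one cohort meets that step soon after allocation and the other after a wait.

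**The case against.** The strongest reply is that the only stated test is paired, so selection on level does no harm to it, and that the study calls itself explorative. The first part is correct and limits the point. A reader might infer that the end-of-wait control mean is shifted by a calculable amount and that the randomised comparison is biased to that extent. The documents do not support this: no between-cohort test is stated, no account-creation rate is given, and the sample size rests on the 10-times rule with no power, SD or effect size to set a shift against.

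A reader might also infer that no primary health outcome is measured before allocation, full stop, or that both cohorts' baselines depend on an account. The first goes beyond the text, because the abstract says the outcomes are taken at intake. The second is wrong for cohort 2.

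Safeguards exist. Participants are phoned within 2 working days, a visit is offered to those who need help, tablets are lent, and contact is possible throughout. These may reduce the loss. Calls can be declined, however, and no route to T0 without an account is described.

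Finally, some people who lose interest during the wait would not answer an emailed questionnaire either. That is ordinary waiting-list attrition. The account step adds harm only through people who would answer but would not open an account. This is fair, and it is also the part of the loss that the plan can remove.

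**Conclusion.** The point holds as one of sequence and access. By the Procedure and Table 1, both health outcomes are first measured after allocation is known, at different steps by cohort; the abstract contradicts this, and the passages must be reconciled. T0 is requested only from account holders, so the control-to-T0 change, and any week-4 comparison between cohorts, describes people who take up the app and not everyone allocated.

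The size of any resulting bias cannot be derived. For the stated paired test it is the missing share times the difference in change between people with and without an account, and neither quantity is given. It is zero if everyone opens an account or if the two groups change alike over the wait. The conclusion assumes that the intake content is as the Procedure lists it. If the full protocol has the health battery at intake, as the abstract implies, the baseline part falls away and the T0 part remains.

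**What to change.** 1. Give everyone the 46-item health battery (the present control questionnaire) at the end of the intake questionnaire, before allocation, as the common baseline.
2. Keep T0 in both cohorts, so that each still has a measurement at the start of use. Send its 46 health items by email at the scheduled time, before onboarding and whether or not an account is later created. Leave only the 10 Rapport Scale items tied to the account.
3. State that the 14-day non-interaction rule does not remove these baseline and end-of-wait data from the control comparison. Otherwise people who never open an account could be asked and then discarded.
4. Align the abstract, the Study Design section and Table 1 with this schedule, including an intake column.

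Cost: intake becomes about 10 to 20 minutes longer, by Table 1's own estimate for the 46 items. For cohort 2 the battery is moved and not added. Cohort 1 answers the health items twice within a short time, at intake and at T0. No new instrument is needed.
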